## **7. STATISTICS AND DATA ANALYSIS**

This will be the first study investigating the effects of intranasal kisspeptin administration on reproductive hormone release in humans. Our previous work in healthy volunteers demonstrates that intravenous kisspeptin increases serum LH (mean 10.2 IU/L and standard deviation 0.4 IU/L), compared with placebo administration (mean 2.0 IU/L, standard deviation 0.1 IU/L) (11), and we predict a similar response following intranasal administration. Therefore, using these data, with  $\alpha = 0.05$ , power = 0.8 and effect size = 0.997, we performed a power calculation resulting in a sample size of 10 participants per group (*Group A* and *Group B*). To allow for dropouts and exclusions (estimated to be around 20%), 12 participants per group (*Group A* and *Group B*) will be recruited. It should be noted that regarding patients with reproductive disorders (*Group C*), the sample size will depend upon the specific disorder. For instance, our previous work demonstrates that the gonadotropin response following kisspeptin administration is similar in patients with polycystic ovary syndrome versus healthy women but augmented in patients with hypothalamic amenorrhoea [unpublished data].

Hormone level data will be assessed for normality and appropriate statistical methods chosen. Continuous data will be reported as measures of central tendency and of spread (e.g., mean and standard error of the mean or median and interquartile range as appropriate). For all study groups, time profiles of hormone levels during the 4-hour study period will be compared using two-way ANOVA with Bonferroni multiple comparison test [if the data is parametric], or Kruskal-Wallis test [if the data is non-parametric]. Mean responses (e.g., maximal increase and area under curve) will be compared using one-way ANOVA with Bonferroni multiple comparison test (*Group A*) and paired t-tests (*Group B* and *Group C*) [if the data is parametric] or Kruskal-Wallis test (*Group A*) and Wilcoxon signed-rank test (*Group B* and *Group C*) [if the data is non-parametric].  $P < 0.05$  will be considered statistically significant.

Data and all appropriate documentation will be stored for a minimum of 10 years after the completion of the study, including the follow-up period.

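### Group A's one-way ANOVA applies one pooled error variance to every contrast, although the protocol's own LH figures put the kisspeptin variance at 16 times the placebo variance, so the precision stated for individual doses will be wrong

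*Protocol*

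**What the plan says.** Section 7 of the protocol fixes the analysis of Group A's summary responses: "Mean responses (e.g., maximal increase and area under curve) will be compared using one-way ANOVA with Bonferroni multiple comparison test", with Kruskal-Wallis if the data are not normal. Time profiles in all three groups go to two-way ANOVA with Bonferroni comparisons. Summary responses in Groups B and C go to paired t-tests or Wilcoxon signed-rank tests.

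The only assumption check is in this sentence: "Hormone level data will be assessed for normality and appropriate statistical methods chosen". Equal variance and sphericity are not mentioned, and neither ANOVA is described as repeated-measures.

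The same section supplies the planning data. Earlier work showed that "intravenous kisspeptin increases serum LH (mean 10.2 IU/L and standard deviation 0.4 IU/L"), "compared with placebo administration (mean 2.0 IU/L, standard deviation 0.1 IU/L"), and for the nasal route "we predict a similar response following intranasal administration".

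Section 3 makes Group A a five-visit crossover: every man receives four doses and placebo.

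**The concern.** A conventional one-way ANOVA estimates one residual variance from all treatments and uses it for each pairwise comparison. That is sound when the treatments have similar spread. The protocol's only figures on spread say otherwise: placebo LH is tight and kisspeptin LH is four times as variable in SD terms. The pooled variance then belongs to no contrast. It is neither the variance of a dose-placebo difference nor that of a dose-dose difference.

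Normality testing does not detect this, and the fallback does not cure it. Kruskal-Wallis is triggered by non-normality rather than unequal spread, ignores the pairing, and is itself sensitive to unequal spread. The paired tests in Groups B and C avoid the problem, so the group with the most contrasts has the weakest error term. At stake are the p-values and intervals reported for each dose in the first human use of this route.

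**Working it through.** **The plan's own figure.** The protocol reports "power = 0.8 and effect size = 0.997" and 10 participants per group. A two-sided paired t-test with standardised difference 0.997, n = 10 and alpha 0.05 has power 0.801, so the 10 is reproduced. It was obtained with a paired test, not with the ANOVA named for Group A.

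**Inputs.** From section 7: SD 0.4 (kisspeptin) and 0.1 (placebo), n = 10. From section 3: five treatments per man. Assumptions: all four doses have SD 0.4, and the within-man correlation r is common to all pairs of visits. The protocol does not give r, so it is varied.

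**Variance ratio.** 0.4² / 0.1² = 0.16 / 0.01 = 16. If both figures were mislabelled standard errors from equal numbers, the ratio would still be 16.

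**True variance of a within-man difference**
- Dose minus placebo: 0.16 + 0.01 − 2r(0.4)(0.1) = 0.17 − 0.08r
- Dose minus dose: 2(0.16)(1 − r) = 0.32(1 − r)

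**Variance that each ANOVA assumes**
- One-way, as written: 2 × (4 × 0.16 + 0.01)/5 = 2 × 0.13 = 0.26, whatever r is.
- Repeated-measures: the average over the ten pairs, [4(0.17 − 0.08r) + 6 × 0.32(1 − r)]/10.

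The SE ratio is the square root of assumed over true variance. At r = 0, √(0.26/0.17) = 1.24 and √(0.26/0.32) = 0.90. In the table the first number is the SE ratio and the bracket is the true rejection rate of an unadjusted nominal 5% test, simulated with 10 men (good to about 0.2 percentage points).

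| r | One-way, dose-placebo | One-way, dose-dose | Repeated-measures, dose-placebo | Repeated-measures, dose-dose |
|---|---|---|---|---|
| 0 | 1.24 (1.8%) | 0.90 (7.7%) | 1.24 (1.8%) | 0.90 (7.7%) |
| 0.5 | 1.41 (0.9%) | 1.28 (1.6%) | 1.07 (3.8%) | 0.96 (5.7%) |
| 0.625 | 1.47 (0.9%) | 1.47 (0.8%) | 1.00 (5.0%) | 1.00 (5.1%) |
| 0.8 | 1.57 (0.7%) | 2.02 (0.1%) | 0.87 (8.5%) | 1.12 (3.0%) |

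The one-way dose-dose ratio equals 1 where 0.32(1 − r) = 0.26, that is r = 0.1875. Below that the SE is too small, above it too large.

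**How much is unequal variance and how much is lost pairing.** The repeated-measures column isolates the first. At r = 0 the whole 1.24 is unequal variance. At 0.5, 1.41 = 1.33 (pairing) × 1.07 (variance). At 0.8, 1.57 = 1.79 × 0.87, so unequal variance there pulls the other way.

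**Pair-specific test for comparison.** The paired t-test on each dose-placebo difference rejected 4.8% to 5.1% of the time over correlations from 0 to 0.8 in the same simulation.

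**Time profiles.** With two arms whose variances stay constant over time, the pooled error gives the treatment contrast its correct variance, 0.17/n at r = 0. The 16:1 ratio alone therefore produces no distortion there. Suppose instead that the kisspeptin variance is 0.16 at k of 17 time points and 0.01 elsewhere (assumption). The assumed variance of a difference at one time is then [17 × 0.01 + 0.16k + 0.01(17 − k)]/17. For k = 4 to 16 the SE ratio is 0.57 to 0.97 at the raised times and 1.66 to 2.84 at the others.

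**The case against.** **The direction is not known.** A reader might infer that dose-placebo errors are always too large and dose-dose errors always too small. The documents do not support that. For the one-way ANOVA as written, the dose-dose SE is too small only below a correlation of about 0.19, and men acting as their own controls may well exceed that. In a repeated-measures version the distortion vanishes at 0.625 and reverses beyond it. This objection stands.

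**The 16:1 ratio is thin evidence.** It describes intravenous serum LH, not maximal increase or area under the curve, and not any particular nasal dose. The SDs also clash with the stated effect size: 8.2/√0.17 = 19.9, whereas 0.997 implies a difference SD of 8.2/0.997 = 8.2. The figures are therefore doubtful, but they are the only ones offered and they argue against a common variance. A reader might let the SD grow with dose and obtain larger distortions, but no dose-specific SD is given.

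**Overall error control is barely touched.** With Bonferroni over all ten pairs and no true differences, the familywise rate at n = 10 is 3.8% to 5.2% for repeated-measures and at most 5.3% for one-way over correlations 0 to 0.8. That is correct. The fault lies in individual contrasts and intervals.

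**The practical effect is small on the protocol's means.** An 8.2 IU/L difference over a pooled SE of √(0.26/10) = 0.16 gives t of about 51. This also stands, although the sample size rests on 0.997, where the SE does matter.

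**It may be settled in an analysis plan.** Sphericity and variance handling often are, and the protocol speaks of choosing appropriate methods. But it goes on to name the tests and ties the choice to normality alone, so the conflict with its own figures is in the text.

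**Conclusion.** The point holds in a limited form. With all doses at SD 0.4, the one-way ANOVA as written gives dose-placebo standard errors 1.24 to 1.57 times too large over correlations 0 to 0.8, partly because it ignores the pairing. Making it repeated-measures removes the lost-pairing part but leaves a ratio between 1.24 and 0.87, the last with a true error rate of about 8.5%. Without a stated correlation the sponsor cannot know which way the test errs.

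The consequence is misstated p-values and intervals for individual doses. A reader might infer that the wrong dose could go forward to Groups B and C. The protocol does not support that, because section 3 selects the dose with the largest maximal LH rise and uses no test. A reader might also infer that every time-profile ANOVA is invalid. Time profiles add a further problem only if variance changes over the four hours, which is plausible but not stated. Summary responses in Groups B and C are unaffected. This should be corrected, but it does not threaten the trial's main conclusion if the effect is anywhere near the one predicted.

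**What to change.** In section 7, replace Group A's one-way ANOVA by a test of each dose against placebo on that pair's own within-man differences, as already planned for Groups B and C, with Holm or Bonferroni adjustment. Alternatively, fit a within-participant model with a separate residual variance for each treatment. For time profiles, take the standard error at each time point from that time's own kisspeptin-minus-placebo differences. State that the variance assumption, as well as normality, decides the error term.

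The change is to analysis wording only; visits, sampling and numbers stay as they are. The price is degrees of freedom: 9 per pair instead of 36 in a pooled repeated-measures analysis. If the variances were in fact equal, with standardised effect 0.997, n = 10 and alpha 0.05/4, power per dose would be 0.54 instead of 0.70. Holm brings it back to about 0.67 if all four doses have that effect, and the treatment-specific-variance model also recovers much of the loss.

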## 2. STUDY OBJECTIVES

### Primary Outcome:

Change in serum LH following intranasal administration of kisspeptin compared to placebo. Blood samples will be taken at baseline (pre-administration) and every 15 minutes for 4 hours.

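### Group A's single-step Bonferroni test is valid but dominated: Holm or step-down Dunnett on the four dose-versus-placebo LH contrasts keeps the same 5% familywise error and never rejects less

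*Protocol*

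**What the plan says.** Protocol section 2 defines the primary outcome as "Change in serum LH following intranasal administration of kisspeptin compared to placebo". Under section 3 (Study Visits, Group A) each man attends five visits and receives four kisspeptin-54 doses and saline in random order.

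For Group A, section 7 compares maximal increase and area under the curve by "one-way ANOVA with Bonferroni multiple comparison test", with Kruskal-Wallis as the non-parametric alternative. It does not say whether Bonferroni covers every pair of conditions or only the doses against placebo.

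The same section sizes Groups A and B with one calculation, at "power = 0.8 and effect size = 0.997", "resulting in a sample size of 10 participants per group", and recruits 12 to allow for losses. It makes no mention of an allowance for multiple testing.

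Section 3 (Group B) takes forward the dose with the largest peak LH rise in the men. That is a ranking; no dose-versus-dose test is named.

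**The concern.** Four doses against one placebo give four primary contrasts in Group A. Single-step Bonferroni holds each of them to the strictest level, 0.05/4, even after other doses have been shown to work. If it is run over all five conditions, the level is 0.05/10, and six of the ten comparisons are dose against dose, which the primary outcome does not ask about.

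The protocol does choose a method here, so this is not detail left for a later document. Better procedures exist at the same error rate. What is at stake is Group A's own conclusion about which intranasal doses raise LH: with about 10 evaluable men, a dose that works may be reported as not shown to work, with nothing useful gained in error control.

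**Working it through.** **Inputs.** From section 7: alpha 0.05, power 0.8, effect size 0.997, 10 evaluable and 12 recruited per group. From section 3: four doses and placebo in every man. Assumptions not in the protocol: two-sided tests; 0.997 is the mean within-man difference divided by its standard deviation (dz); equal variances, so that two dose-placebo differences sharing a placebo visit correlate 0.5.

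**1. The plan's own figure.** For one paired t-test the noncentrality is dz × √n = 0.997 × √10 = 3.153, with 9 df and critical value 2.262. Power is 0.801; at n = 9 it is 0.746. So n = 10 reproduces as a single unadjusted two-sided paired test.

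**2. Bonferroni as named, n = 10.** Same noncentrality, with alpha divided by the number of tests. The pooled within-man error has 4 × (10 − 1) = 36 df.

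| Family | Level | Critical value, 36 df | Power, pooled | Critical value, 9 df | Power, pair-specific |
|---|---|---|---|---|---|
| 4 contrasts | 0.0125 | 2.63 | 0.70 | 3.11 | 0.54 |
| 10 pairs | 0.005 | 2.99 | 0.57 | 3.69 | 0.37 |

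Power is below 0.80 under either family.

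**3. Step-down alternatives over the four contrasts.** Holm starts at Bonferroni's level of 0.05/4 and relaxes to 0.05/3, 0.05/2 and 0.05 after each rejection. It therefore rejects everything Bonferroni rejects, whatever the effect size or correlation. Step-down Dunnett also uses the correlation from the shared placebo visit; its critical values at 36 df are about 2.55, 2.45, 2.30 and 2.03, the first already below Bonferroni's 2.63. Simulated power for a fully active dose, n = 10, other doses inactive:

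| Active doses | Bonferroni-4, pooled | Holm, pooled | Step-down Dunnett, pooled | Holm, pair-specific |
|---|---|---|---|---|
| 1 | 0.70 | 0.70 | 0.72 | 0.55 |
| 2 | 0.70 | 0.72 | 0.74 | 0.57 |
| 3 | 0.70 | 0.75 | 0.77 | 0.61 |
| 4 | 0.70 | 0.79 | 0.80 | 0.67 |

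With all four doses active, the chance of detecting all four is 0.42 with Bonferroni-4 against 0.65 (Holm) or 0.66 (step-down Dunnett). With no dose active, familywise error is 0.043 for Bonferroni-4 and about 0.05 for step-down Dunnett.

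**4. A graded response.** With doses at 50, 75, 90 and 100% of the effect (pooled error, n = 10), Bonferroni-4 gives 0.16, 0.41, 0.59 and 0.70. Step-down Dunnett gives 0.29, 0.52, 0.66 and 0.75. Every dose gains; none reaches 0.80.

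**5. If all 12 complete.** Pooled error (44 df): Bonferroni-10 0.69, Bonferroni-4 0.80, Holm 0.80 to 0.87, step-down Dunnett 0.82 to 0.88. Pair-specific: Bonferroni-4 0.68, Holm 0.68 to 0.80.

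**6. How far 0.997 can be trusted.** Section 7 rests it on data in which kisspeptin "increases serum LH (mean 10.2 IU/L and standard deviation 0.4 IU/L", "compared with placebo administration (mean 2.0 IU/L, standard deviation 0.1 IU/L". The difference is 10.2 − 2.0 = 8.2. The standard deviation of a within-person difference must lie between 0.4 − 0.1 = 0.3 and 0.4 + 0.1 = 0.5, so dz would lie between 8.2/0.5 = 16.4 and 8.2/0.3 = 27.3. No correlation gives 0.997. At the larger values every procedure above has power near 1.

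**The case against.** Bonferroni controls the error rate, and section 7 contains no misstatement on this point. Four stronger readings are tempting, and the protocol does not support them.

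- *The plan tests all ten pairs.* A reader might infer this because it is a common form of the test after an ANOVA. Section 7 names no family, and four dose-placebo contrasts fit its wording equally well. The 0.57 is therefore conditional, and if four contrasts were meant, stepping down adds between nothing (Holm, one active dose) and about 0.10 (all four active).
- *Stepping down restores 80% power with no more men.* At 10 completers this needs all four doses at full effect and a pooled within-man error. Group A is run because the dose-response is unknown.
- *A poor test sends the wrong dose to Groups B and C.* That choice is a ranking and is the same under every procedure here.
- *Changing the multiplicity step is enough.* Section 7 names a one-way ANOVA without saying whether it is repeated-measures. If it were an ordinary one, ignoring that the same men are measured throughout, power at n = 10 with an assumed within-man correlation of 0.5 would be about 0.34 (four contrasts) or 0.20 (ten pairs). That is a larger loss, so the fix has to name the within-participant model as well.

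It is also fair to say that dose-dose comparisons have some interest, since Group A is meant to inform the choice of dose. Estimates with intervals serve that purpose, and the selection rule uses no test.

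**Conclusion.** The concern stands as one of efficiency, not validity. That Holm dominates single-step Bonferroni over the same family is a mathematical fact and rests on none of the power inputs; step-down Dunnett shares the advantage if variances are equal within men.

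The size is conditional on dz = 0.997. At 10 completers with pooled error, the gain over four-contrast Bonferroni for a fully active dose is about 0.02 to 0.10 with step-down Dunnett and 0 to 0.09 with Holm. With pair-specific tests, Holm gains about 0.01 to 0.13. If ten pairs were intended, cutting to four contrasts adds a further 0.13 (0.57 to 0.70, pooled). Since 0.997 is not supported by the plan's own means and standard deviations, the true gain could be negligible if the effect is very large.

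The consequence is confined to Group A's statements about which doses raise LH. The change is worth making because it costs almost nothing.

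**What to change.** In section 7, state that the Group A confirmatory family is the four dose-versus-placebo LH contrasts, estimated from a within-participant (repeated-measures) analysis and tested at 5% familywise by step-down Dunnett. Use Holm instead if each contrast has its own variance, or if the data call for a paired non-parametric test. Report dose-dose differences as estimates with confidence intervals, without tests. Any power statement for Group A should give the range over the number of active doses and not a single 80%.

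Cost: a sentence or two of protocol text, with no extra men, visits or samples. The one loss is that simple simultaneous intervals do not match a step-down test, so intervals would be given unadjusted or single-step and labelled as such.

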## **8. REGULATORY ISSUES**

### **8.1. ETHICS APPROVAL**

The Study Coordination Centre has obtained approval from the Riverside Research Ethics Committee, London, UK (ref: 17/LO/1504) [studies in men] and the West London Research Ethics Committee, London, UK (ref: 12/LO/0507) [studies in women] and Health Research Authority (HRA). The study must also receive confirmation of capacity and capability from each participating NHS Trust before accepting participants into the study or any research activity is carried out. The study will be conducted in accordance with the recommendations for physicians involved in research on human subjects adopted by the 18th World Medical Assembly, Helsinki 1964 and later revisions.

### **8.2. CONSENT**

Consent to enter the study must be sought from each participant only after a full explanation has been given, an information leaflet offered, and time allowed for consideration. Signed participant consent should be obtained. The right of the participant to refuse to participate without giving reasons must be respected. After the participant has entered the study the clinician remains free to give alternative treatment to that specified in the protocol at any stage if he/she feels it is in the participant's best interest, but the reasons for doing so should be recorded. In these cases, the participants remain within the study for the purposes of follow-

up and data analysis. All participants are free to withdraw at any time from the protocol treatment without giving reasons and without prejudicing further treatment.

### **8.3. CONFIDENTIALITY**

The Chief Investigators will preserve the confidentiality of participants taking part in the study and is registered under the Data Protection Act. Data will be pseudonymised. Data will not be transferred to a third party.

The results are likely to be published in the six months following the study. The results might be reported in internal reports, peer reviewed scientific journals, other publications or as part of conference presentations. Confidentiality will be ensured at all times, and participants will not be identified in any publication. At the end of the study, the results of the study can be made available to the participant, or their GP should they wish.

### **8.4. INDEMNITY**

Imperial College London holds negligent harm and non-negligent harm insurance policies which apply to this study.

### **8.5. SPONSOR**

Imperial College London will act as the main Sponsor for this study. Delegated responsibilities will be assigned to the NHS trusts taking part in this study.

### **8.6. FUNDING**

This study will be funded from [name] NIHR Research Professorship and Senior Investigator Award. Participants will receive £100 per study visit on completion of the study to cover expenses including travel costs, time off work and lost earnings. The investigators do not receive any payment for this study.

### **8.7. AUDITS**

The study may be subject to audit by Imperial College London/ Imperial College Healthcare NHS Trust under their remit as sponsor and other regulatory bodies to ensure adherence to GCP and the UK Policy Framework for Health and Social Care Research.

## **9. STUDY MANAGEMENT**

The day-to-day management of the study will be led by [name], under the supervision of the Chief Investigators ([name] [name] and [name] [name]).

## **10. PUBLICATION POLICY**

We aim to disseminate data generated during the study via publication in peer reviewed medical journals, presentation at conferences and publication in the lay press as appropriate. During publication the data will be completely anonymised and no personal information will be published. Participant confidentiality will be maintained throughout. Participants and their GPs (with the participant's consent) will be provided with a copy of published data should they wish.

